### 4.5.2.2 Secondary outcomes

1. 50% reduction in eGFR

This analysis will exclude anyone without a baseline eGFR measurement. We will be cautious when interpreting our analysis of eGFR outcomes as this is unlikely to be generalisable to the general population and only to people who had an indication for baseline eGFR testing (e.g. comorbidities, drugs).

Baseline eGFR will be defined as the mean primary care eGFR calculated from serum creatinine using the CKD-EPI equation from 18 months before the index date up to 14 days before the index date (or 14 days before hospital admission date for hospitalised COVID-19 cases).

Primary care eGFR measurements will be followed-up monthly from the index date, until criteria for the outcome endpoint is met (50% reduction in eGFR from the baseline eGFR).

The OpenSAFELY platform is currently only able to extract a predefined number of measures for any variable (i.e., it is not possible to extract all available measures); we will therefore extract and use the last eGFR measure for every calendar month in follow-up.

Incident ESRD (i.e. dialysis or kidney transplant primary care codes, or ICD-10 or procedural codes from SUS, or eGFR  $<15\text{ml/min/1.73m}^2$  in primary care) will also be included in the outcome definition.

We will also consider assessing changes in eGFR trajectory using slopes.

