#### **4.4.4 Follow-up start**

By using index dates 28 days after first recording of SARS-CoV-2 infection (i.e., date of testing in SGSS, date of primary care coding, or date of admission on SUS), we will be able to look back and further stratify the exposure by measures of SARS-CoV-2 severity (i.e. community, hospitalisation, critical care admission etc.).

For analyses comparing people after SARS-CoV-2 infection to a historical comparator group from 2018-2019, the matched historical comparators will be followed-up from exactly two years before the index date.

For analyses comparing people hospitalised for COVID-19 with an unmatched historical group of individuals hospitalised for pneumonia from 2018-2019, we will follow all eligible individuals from 28 days after their admission date for pneumonia.

For analyses comparing people after SARS-CoV-2 infection to a matched contemporary comparator group, we will follow all eligible individuals from the index date.

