## 4.5 Study measures

### 4.5.1 Exposure

We will identify recorded SARS-CoV-2 infection using data from SGSS, primary care records and SUS. We will include all codes indicative of SARS-CoV-2 infection. SGSS contains the date of an individual's earliest positive SARS-CoV-2 test results from Pillar 1

(NHS and Public Health England laboratories) and Pillar 2 (commercial partners) between 1 February 2020 to the most recent available time point (i.e. the COVID-19 pandemic era).

Individuals meet criteria for inclusion in the COVID-19 exposed group if they:

- Tested positive for SARS-CoV-2 infection in SGSS
- Had a primary care code indicative of SARS-CoV-2 infection
- Discharged from hospital with an International classification of Diseases Version 10 (ICD-10) code in SUS indicative of COVID-19

The index date for those exposed to COVID-19 will be from 28 days after first recording of SARS-CoV-2 infection (i.e., after the earliest date of the record of a positive test in SGSS, primary care coding, or admission in SUS).

Looking at all identified SARS-CoV-2 infections will allow us to investigate how many adverse kidney outcomes can be prevented by preventing SARS-CoV-2 infection altogether through comparisons with people from the general population without known infection. We will also be able to investigate whether outcomes vary based on infection severity (hospitalisation, critical illness, mechanical ventilation and AKI [including requiring RRT]) as well as calendar time and vaccination status through further stratification based on morbidity coding (ICD-10 codes) from SUS. We will categorise people as i) unvaccinated if they had not received any vaccine dose at least 7 days before first recording of SARS-CoV-2 infection, ii) single dose vaccinated if they had received one vaccine dose at least 7 days before first recording of SARS-CoV-2 infection, iii) double vaccinated if they had received two vaccine doses at least 7 days before first recording of SARS-CoV-2 infection, and iv) more than double vaccinated if they had received more than two vaccine doses (including booster doses) at least 7 days before first recording of SARS-CoV-2 infection.

Hospitalised COVID-19 cases will be further investigated through a separate comparison with a historical group. Additional levels of exposure for those hospitalised will include critical care admission, mechanical ventilation, acute KRT and AKI, determined from ICD-10 and procedural codes in SUS.

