### 4.5.3 Covariates

Covariates have been determined using a directed acyclic graph (DAG) (Figure 2): demographic (age, sex), geographic region, deprivation, ethnicity, smoking, body mass index (BMI) and existing comorbidities.

For the matched historical comparison groups, we will extract covariable data as of 28 days before the index date (i.e. on the date of first recording of infection) on OpenSAFELY.

[figure not shown]

**Figure 2** Causal diagram for SARS-CoV-2 infection and end-stage renal disease

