#### **4.5.3.3 Clinical**

We will describe several clinical conditions including: cancer, cardiovascular diseases, chronic liver disease, diabetes mellitus, hypertension and immunosuppressive diseases.

We will describe baseline eGFR for each individual based on the mean eGFR recoded from 18 months to 14 days before the index date. As with follow-up eGFR, it is not possible to obtain infinite serial eGFR measurements from OpenSAFELY and so the final eGFR measurement of each calendar month before the index date (up to 18 months before the cohort start date) will be recorded for each individual. eGFR will be calculated using the CKD-EPI equation using serum creatinine measurements without adjustment for ethnicity. Baseline eGFR will be classified as follows:

1.  $\geq 105$  ml/min/1.73m^2
2. 90-104 ml/min/1.73m^2
3. 75-89 ml/min/1.73m^2
4. 60-74 ml/min/1.73m^2
5. 45-59 ml/min/1.73m^2 (CKD stage 3A)
6. 30-44 ml/min/1.73m^2 (CKD stage 3B)
7. 15-29 ml/min/1.73m^2 (CKD stage 4)
8. No eGFR measurement

We will define smoking status based on most recent primary care coding as non-smokers, ex-smokers or current smokers. We will assume that individuals with no record of smoking status are non-smokers as smoking is less common than not smoking (approximately 14% of the UK adult population were smokers in 2019). However, we will run a sensitivity analysis restricting to those with known smoking status.

BMI will be calculated using the most recent height and weight closest to the index date, then categorised as: underweight ( $<18.5\text{kg/m}^2$ ), normal weight ( $18.5\text{--}24.9\text{kg/m}^2$ ), overweight ( $25.0\text{--}29.9\text{kg/m}^2$ ), obese ( $\geq 30.0\text{kg/m}^2$ ) and undocumented (assumed to be normal in main analyses).

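### The baseline eGFR window closes 14 days after infection (or pneumonia admission) in every ill group except hospitalised COVID-19 cases, and two sections define it differently

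*Protocol*

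**What the plan says.** Section 4.5.1 fixes the time origin: "The index date for those exposed to COVID-19 will be from 28 days after first recording of SARS-CoV-2 infection". Section 4.4.4 gives the reason for the delay, which is to let severity be classified by looking back. For the pneumonia comparison the same section says "we will follow all eligible individuals from 28 days after their admission date for pneumonia".

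Section 4.5.2.2 defines baseline eGFR as a mean of primary care values over "18 months before the index date up to 14 days before the index date (or 14 days before hospital admission date"; the exception in full reads "or 14 days before hospital admission date for hospitalised COVID-19 cases". An event is a fall to half of that mean, and people with no baseline value are left out of the analysis.

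Section 4.5.3.3 describes the same variable as "based on the mean eGFR recoded from 18 months to 14 days before the index date", with no exception for hospitalised cases. It keeps the last reading of each calendar month.

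Section 4.5.3 uses another anchor for the matched historical groups: "we will extract covariable data as of 28 days before the index date (i.e. on the date of first recording of infection"). The lay summary (Section 1.2) describes the outcome as a loss of at least half relative to kidney function before COVID-19.

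**The concern.** Baseline is meant to describe the kidneys before the illness. As written, it can include readings from the first two weeks of the illness in non-hospitalised cases and pneumonia comparators. General-population comparators have no recorded infection at the match date, so any error is differential. In the hospitalised comparison, the COVID-19 and pneumonia groups have baselines that stop at different points relative to admission.

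The variable has three uses. It is the denominator of the 50% decline, an adjustment covariate in the second model of Section 4.6.2 (which includes the primary ESRD outcome), and a stratifier in Section 4.6.3.

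If acute illness lowers eGFR, a baseline that is too low makes a 50% fall harder to reach. In non-hospitalised cases that would hide events and move the hazard ratio towards the null. In pneumonia comparators it would remove comparator events and raise the COVID-19 versus pneumonia hazard ratio.

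The disagreement between Sections 4.5.2.2 and 4.5.3.3 also means that two programmers could build different baselines for hospitalised cases.

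**Working it through.** The protocol gives no figure for this point. Its only calculated figures are the ESRD power estimates in Section 5, which do not depend on the baseline window. For the record, the 88% for a hazard ratio of 1.6 with 200,000 exposed is reproduced by a two-sided 5% comparison of 0.032% with 0.02%, at five comparators per exposed person.

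**Step 1: closing day of the window.** Inputs: index date at day +28 (Sections 4.4.4 and 4.5.1); pneumonia follow-up start at admission day +28, read as that group's index date (Section 4.4.4); window end at index minus 14 days. Closing day = 28 − 14 = +14.

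| Group | Section 4.5.2.2 | Section 4.5.3.3 |
|---|---|---|
| Non-hospitalised COVID-19 | day +14 after first record | day +14 after first record |
| Hospitalised COVID-19 | day −14 before admission | day +14 after first record |
| Pneumonia comparators | day +14 after admission | day +14 after admission |
| Matched general population | day +14 after match date, no recorded infection at that date | the same |

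Under Section 4.5.2.2 the two hospitalised groups differ by 14 − (−14) = 28 days.

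**Step 2: share of the window affected.** Eighteen months is 18 × 30.4375 ≈ 548 days. The window opens at 28 − 548 = day −520 and closes at day +14, a length of 534 days. The share after infection or admission is 14/534 = 2.6%.

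**Step 3: effect on the event threshold.** Let T be the true pre-illness eGFR and k the number of readings, one of which is low by a fraction d. The baseline is B = T(1 − d/k). An event needs eGFR at or below B/2, so the fall required from T is 1 − B/(2T) = 0.5 + d/(2k). The values T = 60 and d = 0.25 are assumptions:

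- k = 1: B = 45, threshold 22.5 instead of 30, fall needed 62.5%.
- k = 4: B = 56.25, threshold 28.1, fall needed 53.1%.
- k = 12: B = 58.75, threshold 29.4, fall needed 51.0%.

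For d from 0.10 to 0.50, the fall needed runs from 55% to 75% with one reading and from 50.4% to 52.1% with twelve.

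**Step 4: which readings survive.** Only the last reading of a calendar month is kept. If infection is recorded on the 5th and GP tests fall on the 3rd and the 15th, the reading of the 15th is kept and that of the 3rd is lost. A person whose only reading falls on days 0 to 14 enters the eGFR analysis because of a post-infection test.

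**The case against.** The date arithmetic is hard to dispute; the case against concerns size and scope. Section 1.3 says blood results come from GP records rather than hospitals, so creatinine taken during an admission does not enter the baseline. For pneumonia comparators, only GP tests within 14 days of admission can contaminate it. Section 2.1 says the risk of AKI in mild or asymptomatic infection is unknown, so a large acute dip in non-hospitalised cases cannot be presumed. Section 6 notes that creatinine may fall after severe illness, which makes the sign less certain, although that passage concerns sustained changes. The 50% decline is a secondary outcome that the protocol already treats cautiously, and baseline eGFR is banded when classified as a covariate. Under Section 4.5.2.2, hospitalised COVID-19 cases are largely protected unless the first record precedes admission by more than 14 days.

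All of this stands and limits the size. It does not remove the defect. The variable also reaches the primary outcome as an adjustment term, and the deviations table reports that only fully adjusted models were run. That table does not change the window.

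Three stronger readings are not supported:

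- A reader might infer that the rule explains the absence of effect in non-hospitalised cases mentioned in the deviations table. The direction could match, but nothing in the document shows that it did.
- A reader might take the inflation of the pneumonia comparison as established. It depends on acute illness lowering eGFR and on an unknown number of early GP tests.
- A reader might conclude that BMI, taken from the "most recent height and weight closest to the index date", is measured after the illness. That holds only for people measured in the 28 days after infection. No passage places smoking or comorbidities after infection.

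**Conclusion.** The rule is wrong as written and should be fixed. Followed literally, it gives a baseline that includes post-infection or post-admission days in two groups and not in a third. It conflicts with the stated aim of measuring loss from before COVID-19, and it is defined inconsistently in Sections 4.5.2.2 and 4.5.3.3.

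The date conclusion needs only the protocol's own anchors and the reading of pneumonia follow-up start as that group's index date. The direction of bias is conditional on acute illness lowering eGFR. The average effect is probably small but cannot be fixed from the document, because the frequency of GP tests on days 0 to 14 is not given. The effect is concentrated in people with one or two readings.

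**What to change.** In every group, end the baseline eGFR window 14 days before the date of first recording, the match date or the pneumonia admission. For hospitalised COVID-19 cases, use the earlier of first record and admission. Apply this cut before taking the last value of each calendar month. Make Sections 4.5.2.2 and 4.5.3.3 state the same rule. At most, add that BMI uses the pre-infection date of Section 4.5.3 in all comparisons.

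Before extraction, this costs two sentences and a date offset. A few people lose their only baseline value and leave the eGFR analysis. The appended deviations table describes completed analyses and no data access after 30 June 2024, so a re-run may need renewed access. In that case, state which window the code used and, if access allows, report a sensitivity analysis with the re-anchored window.

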## 2. AKI

We will identify episodes of hospitalisation with AKI through ICD-10 codes in any diagnostic position in SUS after the index date.

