# 1. Lay summary

## 1.1 Background

People who require hospital admission for COVID-19 usually have severe lung infection which means they can struggle to maintain oxygen levels. However, other organs can also be affected, with the kidneys being among the most common. Around a third of people admitted to hospital with COVID-19 develop kidney damage (known as acute kidney injury or AKI); of these, around 10% develop such severe AKI that they require short-term dialysis (treatments to clear out toxins and excess fluid from their bodies). The reasons for this AKI are yet to be definitively understood.

It is not unusual for AKI to complicate any severe illness (such as life-threatening infections or trauma), especially in people who have other medical problems such as diabetes, chronic kidney disease (CKD) or heart failure. We do not know whether AKI related to COVID-19 just reflects this or whether it is because of processes directly related to COVID-19 infection itself.

While AKI is often recoverable, it can sometimes lead to worsening long-term kidney function. Chronic kidney disease is diagnosed when kidney function declines to less than 60% of what it should be. In some cases, chronic kidney disease can lead to permanent kidney failure requiring long-term dialysis (often involving attending a dialysis unit three-times a week for four hours each time), or a kidney transplant. Even without kidney failure, chronic kidney disease is an important risk factor for several other complications including heart disease and death. The complications caused by chronic kidney disease place considerable stress on the NHS and it is important that we know what to expect to be able to ensure that services are planned with sufficient capacity to cope. For example, growing numbers requiring dialysis has a devastating impact on quality of life for those people and will require investment in the workforce and infrastructure. It can also mean more people requiring hospital admissions for heart attacks.

One way of determining what happens to kidney function after COVID-19 is to analyse readily-available health records collected from day-to-day patient care. A recent study of

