## 1.2 Methods

Our study will include adults not already on dialysis and not already having received a kidney transplant. We will compare people with and without COVID-19 for differences in the rates of the following kidney complications:

1. Newly-diagnosed kidney failure (i.e. new dialysis or kidney transplant, or loss of kidney function down to less than 15% of what it should be),
2. At least 50% loss in kidney function from before they developed COVID-19,
3. Further AKI (suggesting their kidneys are more susceptible to future damage).

We will be able to determine whether outcomes vary based on the severity of COVID-19 (i.e. based on whether people required hospitalisation, intensive care, a ventilator, dialysis or had AKI), based on time (e.g. during peaks, after widespread use of effective anti-COVID-19 drugs such as steroids), and based on their levels of vaccination.

In our statistical analysis, we will account for factors such as age, sex, ethnicity, socioeconomic deprivation, smoking, BMI, and pre-existing medical problems such as diabetes.

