## 2.2 COVID-19 and CKD

Individuals are primarily diagnosed with CKD when they are found to have an estimated glomerular filtration rate (GFR) (eGFR) persistently  $< 60\text{ml/min/1.73m}^2$  over at least three months. eGFR is usually calculated from serum creatinine, an easily assayed endogenous marker of kidney function but one that is affected by a range of factors related to both its synthesis and excretion such as age, sex, diet, muscle mass, renal tubular secretion, gut loss, muscle catabolism and genetic ancestry. CKD can also be diagnosed by urinary albumin creatinine ratio  $>3\text{ mg/mmol}$  or in the presence of a structural kidney abnormality (e.g. polycystic kidneys or dysplastic kidneys).

Trajectories of eGFR can vary and progressive decline to  $<15\text{ ml/min/1.73m}^2$  results in end-stage renal disease (ESRD) (also known as “kidney failure”) with long-term KRT required to sustain life (in the form of dialysis or kidney transplantation). In addition to ESRD, CKD is associated with increased all-cause mortality, cardiovascular mortality and morbidity, and AKI. Complications of CKD include anaemia, hyperkalaemia, hypervolaemia, altered pharmacokinetics, and secondary hyperparathyroidism^7. CKD is common, affecting 8.5% of the UK population, and is associated with a substantial burden on healthcare costs.

AKI is a risk factor for CKD. After SARS-CoV-2 infection, tubular injury, de novo immune-mediated processes (such as collapsing glomerulopathy), or direct infection of kidney parenchyma might independently cause additional insults leading to long-term kidney

disease. In addition, pre-existing CKD is an independent risk factor for severe outcomes in COVID-19, plausibly leading to accelerated renal decline in those most at risk.

Given the scale of COVID-19 hospitalisation, including COVID-19-related-AKI, there is a pressing need to understand whether this will lead to an increased burden of CKD and its complications on health systems, given the potential stresses on resources that these will incur.

There has been a gradual increase in the number of studies focusing on post-COVID-19 complications, and some of these include the incidence or progression of kidney diseases.

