### 3. Objectives

Overall, our aim is to investigate long-term kidney outcomes after recorded SARS-CoV-2 infection in the general population.

Our specific objectives are:

1. To describe the relative and absolute rates of ESRD (primary outcome) after recorded SARS-CoV-2 infection compared to both contemporary and historical groups, stratified by:
  - a. Hospitalisation for COVID-19
  - b. Critical care admission for COVID-19
  - c. Mechanical ventilation for COVID-19
  - d. Acute KRT associated with COVID-19
  - e. AKI associated with COVID-19
2. To describe the relative and absolute rates of a 50% reduction in eGFR, incident AKI, and death (secondary outcomes), after recorded SARS-CoV-2 infection compared to both contemporary and historical groups, stratified by:
  - a. Hospitalisation for COVID-19
  - b. Critical care admission for COVID-19
  - c. Mechanical ventilation for COVID-19
  - d. Acute KRT associated with COVID-19
  - e. AKI associated with COVID-19
3. To describe the relative and absolute rates of these outcomes after hospitalisation for COVID-19 compared to a historical hospitalised group, stratified by:
  - a. Critical care admission for COVID-19
  - b. Mechanical ventilation for COVID-19

- c. Acute KRT associated with COVID-19
  - d. AKI associated with COVID-19
- 4. To describe the relative and absolute rates of outcomes after recorded SARS-CoV-2 infection compared to both contemporary and historical groups stratified by:
  - a. Baseline eGFR
  - b. Diabetes
  - c. Age
  - d. Sex
  - e. Ethnicity
  - f. Socioeconomic deprivation
- 5. To describe the relative and absolute rates of outcomes after recorded SARS-CoV-2 infection compared to both contemporary and historical groups additionally stratified by:
  - a. Calendar time
  - b. Vaccination status

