### 4.4.1 Exposure group

Our exposure group will comprise people with recorded SARS-CoV-2 infection identified using data from SGSS, primary care records or SUS who remain alive 28 days after the first recording of infection (i.e. 28 days after date of testing positive in SGSS, coding in primary care records, or admission on SUS) (index date) (Figure 1).

Anyone coded in primary care or SUS to be receiving chronic dialysis or kidney transplant or with  $\text{eGFR} < 15 \text{ ml/min/1.73m}^2$  (i.e. anyone with ESRD or CKD Stage 5) at the time of first recording of SARS-CoV-2 infection will be excluded.

A secondary analysis will investigate individuals who remain alive 28 days after the date of first hospital admission coded for COVID-19 in SUS. Anyone coded in primary care or SUS to be receiving chronic dialysis or kidney transplant or with  $\text{eGFR} < 15 \text{ ml/min/1.73m}^2$  (i.e. anyone with ESRD or CKD Stage 5) at the time of hospital admission will be excluded.

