### 4.6.2 Main analysis

Our statistical analysis plan has been informed by our DAG (**Figure 2**). The DAG has been developed based on assumptions about the causal relationship between SARS-CoV-2 infection and the study outcomes, although it may be limited by currently incomplete understanding. The DAG includes unobserved factors which may be sources of residual confounding (such as socioeconomic factors and comorbidities), as well as sources of

outcome misclassification (i.e. unobserved eGFR decline) and death post-SARS-CoV-2 infection as a competing outcome.

We will use Cox regression models to estimate cause-specific hazard ratios and 95% confidence intervals for ESRD for individuals after SARS-CoV-2 infection, stratified by hospitalisation, critical care admission, mechanical ventilation, acute KRT and AKI, compared to individuals in the i) historical and ii) contemporary comparator groups. The comparator groups have been matched on age, sex, region, socioeconomic deprivation and date.

On the basis of minimum sufficient adjustment sets from our DAG, we will run sequential regression models, i) adjusted for age, sex, socioeconomic deprivation, ethnicity, smoking and BMI and, ii) additionally adjusted for baseline eGFR, cancer, cardiovascular diseases, chronic liver disease, diabetes mellitus, hypertension and immunosuppressive diseases.

We will use robust standard errors to account for clustering by GP practice as well as on individuals as there may be overlap between those in the recorded SARS-CoV-2 infection groups and the historical comparison group (although the time periods are non-overlapping). We will assume people with missing BMI are not obese and people without a documented smoking status are non-smokers.

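### Earlier hospital-coded AKI is neither excluded nor adjusted for, so part of the AKI hazard ratio may reflect prior susceptibility rather than COVID-19

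*Protocol*

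**What the plan says.** **Outcome.** Section 4.5.2.2 defines AKI in one sentence: "We will identify episodes of hospitalisation with AKI through ICD-10 codes in any diagnostic position in SUS after the index date". It sets no look-back, wash-out or first-ever rule. Under section 4.4.5, follow-up stops at the first record of the outcome under study, so the event is the first AKI admission after index, whatever came before.

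**Label.** Objective 2 in section 3 lists "a 50% reduction in eGFR, incident AKI, and death (secondary outcomes". The lay summary (section 1.2) describes the same outcome as "Further AKI (suggesting their kidneys are more susceptible to future damage". The first suggests new disease and the second recurrence.

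**Entry criteria.** Section 4.4.1 excludes "Anyone coded in primary care or SUS to be receiving chronic dialysis or kidney transplant or with" an eGFR below 15 ml/min/1.73m². Sections 4.4.2 and 4.4.3 apply the same exclusion to the matched comparators. A past AKI admission excludes nobody.

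**Adjustment.** The first model in section 4.6.2 contains demographic factors, deprivation, ethnicity, smoking and BMI. The second is "additionally adjusted for baseline eGFR, cancer, cardiovascular diseases, chronic liver disease, diabetes mellitus, hypertension and immunosuppressive diseases". Earlier AKI is in neither, nor is it among the clinical covariates of section 4.5.3.3, the interactions of section 4.6.3 or the sensitivity analyses of section 4.6.4. The deviations table does not add it. AKI before follow-up appears only as a severity level of the COVID-19 or hospital episode.

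**Background.** Section 2.2 states that "AKI is a risk factor for CKD", and section 1.1 adds: "While AKI is often recoverable, it can sometimes lead to worsening long-term kidney function".

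**The concern.** The Protocol's own background makes AKI history a natural candidate confounder. Section 2.1 ties AKI to comorbidity, age and deprivation, and reports pre-existing CKD as strongly associated with AKI and kidney replacement therapy in patients admitted with COVID-19. Section 2.2 calls pre-existing CKD an independent risk factor for severe COVID-19. People prone to AKI may therefore be over-represented among hospitalised cases, while the comparators in the main analysis come from the general population, matched on demographic and area factors.

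The planned covariates stand in for this history only in part. Baseline eGFR is a mean of primary care values from 18 months to 14 days before index. AKI is often recoverable, so a past episode may leave little trace in that mean. People with no value form a category of their own, in which eGFR says nothing about the kidney.

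The AKI outcome also carries weight. Section 6 relies on ESRD and hospitalised AKI as outcomes less open to the testing biases that affect eGFR. That support is weaker if the AKI hazard ratio partly reflects who had AKI before.

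**Working it through.** **Figures in the Protocol.** There is none on earlier AKI: no prevalence in any arm, no recurrence risk and no power statement for the AKI outcome. The only power figures, in section 5, concern ESRD. They can be reproduced (a two-sided comparison of two proportions at 5:1 gives 87.5% for 200,000 exposed and a hazard ratio of 1.6, against 88% in Table 1), but they have no bearing on this point.

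**Is earlier AKI handled anywhere?** The entry exclusions, covariates, both models, interactions, sensitivity analyses and deviations table were read in turn. It appears in none of them.

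**Size under stated assumptions.** For a binary confounder left out of the model:

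bias factor = (1 + p1 × (RR − 1)) / (1 + p0 × (RR − 1))

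- p1, p0: prevalence of earlier AKI in exposed people and in comparators. Both are assumed.
- RR: risk ratio of earlier AKI for later AKI that remains after the planned adjustment. Assumed to be 2, 3 or 5.

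| p1 vs p0 | RR = 2 | RR = 3 | RR = 5 |
|---|---|---|---|
| 3% vs 3% | 1.00 | 1.00 | 1.00 |
| 2% vs 1% | 1.02/1.01 = 1.01 | 1.04/1.02 = 1.02 | 1.08/1.04 = 1.04 |
| 5% vs 2% | 1.05/1.02 = 1.03 | 1.10/1.04 = 1.06 | 1.20/1.08 = 1.11 |
| 10% vs 3% | 1.10/1.03 = 1.07 | 1.20/1.06 = 1.13 | 1.40/1.12 = 1.25 |
| 15% vs 3% | 1.15/1.03 = 1.12 | 1.30/1.06 = 1.23 | 1.60/1.12 = 1.43 |

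Two cautions apply. First, for an adjusted hazard ratio the gap between p1 and p0 should be the one left after matching and adjustment. That is probably smaller than the crude gap, so the lower rows of the table are the less likely ones, and 1.43 is the extreme corner. Second, RR here concerns later AKI only, so the table says nothing about ESRD or eGFR decline.

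**The case against.** **Recurrence is in scope.** AKI is episodic, the lay summary openly speaks of further AKI, and *incident* can be read as a new episode after index. This stands: counting a recurrence is not in itself an error. What remains is that the two labels describe different quantities, and the plan cannot separate them because earlier AKI is never ascertained.

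**Adjustment removes part of the problem.** Baseline eGFR, diabetes, hypertension and cardiovascular disease all carry some of the information. This stands too. Bias arises only if earlier AKI still differs between the arms after adjustment, and the Protocol does not show that it does.

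**The pneumonia comparison helps.** Comparing people hospitalised with COVID-19 with people hospitalised with pneumonia probably balances AKI history better. It does not adjust for that history either. Section 4.6.2 acknowledges residual confounding, but from unobserved factors, whereas earlier AKI can be observed in SUS.

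**Stronger readings that the Protocol does not support.** A reader might infer that AKI is named as a cause of CKD. Section 2.2 says risk factor; the nearer wording is in the lay summary and says only that AKI can sometimes worsen long-term function. A reader might also infer that the hazard ratios for AKI, ESRD and 50% eGFR decline are all biased upward. For ESRD nothing has been quantified. For eGFR decline the direction is open: people without a baseline value are excluded from that analysis, and a recent AKI that lowered the baseline mean would also lower the eGFR at which a 50% fall is reached.

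**Conclusion.** The omission is real, and its effect is conditional. Earlier hospital-coded AKI is a plausible confounder that the plan neither excludes nor adjusts for. It matters mainly for the secondary AKI outcome in hospitalised cases against general-population comparators. Part of that hazard ratio may reflect earlier susceptibility; the Protocol does not establish that it does.

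Under the assumed ranges the inflation runs from about 1.01 to 1.43, and it is nil if prevalence is equal after adjustment. These factors rest on assumed prevalences and risk ratios, not on any figure in the Protocol. Effects on ESRD and 50% eGFR decline are possible but not quantified. Separately, the labels in objective 2 and in the lay summary do not agree, and the definition does not support *incident* in the sense of a first AKI.

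**What to change.** 1. Extract AKI-coded SUS admissions before the date of first SARS-CoV-2 recording, or before the matched date or the pneumonia admission date, with the same look-back length in every arm.
2. Do not adjust for AKI in the 28 days between that date and index. It may be a consequence of the infection and is already an exposure level.
3. Add earlier AKI admission (yes/no) to the second model in section 4.6.2.
4. For the AKI outcome, also report the hazard ratio in people with no earlier AKI admission. Use *incident* only for that result, and align section 1.2 with objective 2.

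**Cost.** One extra covariate, from a data source already in use and an AKI code list already needed for the outcome. The look-back is limited by the SUS history available, and the subset without earlier AKI will have fewer events. If a new extraction is not possible, correcting the label and stating the limitation need no data.
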